## Abstract

**Background:**

High-intensity interval training (HIIT) is an effective strategy for improving a variety of health outcomes within the school setting. However, there is limited research on the implementation of school-based HIIT interventions and the integration of HIIT within the Health and Physical Education (HPE) curriculum. The aims of the *Making a HIIT* study are to: 1) describe the methodology and evaluate the feasibility of co-designing HIIT workouts with students and teachers in HPE; 2) determine the effect of co-designed HIIT workouts on cardiorespiratory and muscular fitness, and executive function; 3) understand the effect of co-design on students’ motivation, enjoyment, and self-efficacy towards the workouts; and 4) evaluate the implementation of the intervention.

**Methods:**

Three schools will participate. Within each school, three different groups will be formed from Year 7 and 8 classes: 1) Co-Designers; 2) HIIT Only; and 3) Control. The study will include two phases. In phase one, Group 1 will co-design HIIT workouts as part of the HPE curriculum using an iterative process with the researcher, teacher, and students as collaborators. This process will be evaluated using student discussions, student surveys, and teacher interviews. In phase two, Groups 1 and 2 will use the co-designed 10-minute HIIT workouts in HPE for 8-weeks. Group 3 (control) will continue their regular HPE lessons. All students will participate in cardiorespiratory fitness, muscular fitness, and executive function assessments before and after the HIIT program or control period. Students will complete questionnaires on their motivation, enjoyment, and self-efficacy of the workouts. Differences between groups will be assessed using linear regressions to account for covariates. Heart rate and rating of perceived exertion will be collected during each HIIT session. The implementation will be evaluated using the Framework for Effective Implementation. Ethical approval was granted by the University of Queensland Human Research Ethics Committee and other relevant bodies.

**Discussion:**

This study will be the first to co-design HIIT workouts with teachers and students within the HPE curriculum. As this study relies on co-design, each HIIT workout will differ, which will add variability between HIIT workouts but increase the ecological validity of the study.

**Trial registration:**

ACTRN, *ACTRN12622000534785*, Registered 5 April 2022 – Retrospectively registered, https://www.anzctr.org.au/ACTRN12622000534785.aspx

**Supplementary Information:**

The online version contains supplementary material available at 10.1186/s12887-022-03440-w.

## Background

Physical inactivity is an important global issue as a high proportion of children and adolescents are not achieving the recommended levels of physical activity for health benefits [1, 2]. Evidence suggests that increasing vigorous physical activity is particularly important as it could be driving health benefits [3, 4]. High-intensity interval training (HIIT) is a method of acquiring vigorous physical activity and includes short bouts of high-intensity exercise interspersed with recovery periods [5]. HIIT is becoming a popular tool for physical activity acquisition in schools and HIIT interventions have been linked with improvements in markers of body size and composition, blood biomarkers, and cardiorespiratory fitness [6]. HIIT is also structured similarly to children’s intermittent patterns of physical activity [7] and can offer opportunities to facilitate learning in health and physical education (HPE) lessons [8].

Schools are an opportune environment to implement HIIT interventions as they can reach a large proportion of adolescents, have existing facilities, and staff capable of facilitating HIIT sessions [9]. Yet, research in schools can present several challenges, including the risk of overburdening teachers or taking away valuable time from the curriculum [9]. To date, most HIIT interventions have not adapted to these challenges and have been conducted during HPE lesson time with no links to the curriculum [6]. Further, very few HIIT interventions have incorporated student and teacher input into the workouts used and none have investigated designing the workouts within the curriculum [6]. Therefore, reviews focused on the topics of school-based HIIT and HIIT in children and adolescents have recommended consulting students and teachers on the design and evaluation of the intervention, and investigating the integration of HIIT within the curriculum [6, 10, 11].

Inherently, integrating HIIT into the curriculum requires the involvement of teachers and students. According to the International Association for Public Participation, engaging end-users in programs exists across a 5-stage continuum ranging from informing to empowering [12]. While stage 5 (empowering) enables the highest level of engagement, it is not always feasible in the curriculum due to time constraints and assessment requirements. However, lower levels of participation, such as involvement or collaboration, where end-users are involved in each phase of the process, are still viewed as beneficial. This active collaboration is often referred to as co-design, which is defined as collective creativity across the entire design process [13, 14]. In the current study, co-design presents a unique opportunity to combine the expertise and lived experiences of researchers, teachers, and students on: 1) the topic of HIIT; 2) the curriculum and school setting; and 3) their physical activity participation. Co-designing HIIT workouts within the curriculum has the potential to support educative outcomes and aligns with several Australian HPE curriculum content descriptions for Year 7 and 8 including, designing personal fitness plans, measuring heart rate, and predicting the benefits of physical activity for health [8, 15]. Further, collaboration with students and teachers in designing the workouts and intervention could increase the chances of implementation and engagement in the school setting as it is tailored to meet the needs and interests of end-users [13].

A limited number of studies have conducted process evaluations to assess the implementation of HIIT interventions in schools [16, 17]. Other studies have reported only selected aspects of process evaluations within their overall results, such as the dosage delivered and received, which could potentially lead to biased results [6, 11]. Process evaluations are important for understanding the connection between implementation and any null, negative, or positive findings [18]. For intervention studies employing co-design, evaluating both the process of co-design and the implementation of the intervention is necessary to draw appropriate conclusions.

### Aims and objectives

The *Making a HIIT* study aims to examine the process and effectiveness of co-designing and implementing HIIT workouts with secondary school students and teachers within HPE. *Making a HIIT* will be conducted in two phases with the following objectives in each phase:

#### Phase one:

To describe the methodology and results of the co-design process to develop HIIT workouts in the HPE curriculum, using the framework outlined by *Leask* et al. [19].To evaluate the feasibility of co-designing HIIT workouts with students and teachers as part of the HPE curriculum.

#### Phase two:

Determine the effect of a HIIT intervention on cardiorespiratory fitness, muscular fitness, and executive function.Determine the effect of the co-design process on students’ enjoyment, self-efficacy, affect, basic psychological needs, and motivation towards the HIIT workouts.Evaluate whether the intervention was implemented as intended through a process evaluation using the framework described by *Durlak and DuPres* [20].

## Methods/design

### Overview

*Making a HIIT* will be completed in two phases, occurring during two subsequent terms in the same school year for each participating school. In phase one, students will co-design HIIT workouts with teachers and researchers as a part of their HPE curriculum (Fig. 1). The process will be evaluated using student discussions, student written feedback, and teacher interviews.

**Fig. 1 Fig1:**
[figure not shown]
Overall Study Schematic. Overall study schematic outlining the lesson topics that will be used in phase one to co-design HIIT workouts with Group 1 and the intervention using the HIIT workouts in phase two. The pre-test and post-test measures are listed under their respective weeks. The data that will be collected during the intervention for the groups performing HIIT (Group 1 and 2) and for the control group (Group 3) are displayed under the eight-week HIIT program. HIIT = high intensity interval training; HPE = health and physical education

In phase two, the HIIT workouts designed in phase one will be implemented using an intervention with a quasi-experimental design. All consenting students will participate in cardiorespiratory fitness, muscular fitness, and executive function assessments before and after the HIIT intervention or control period. They will also complete questionnaires on their motivation, enjoyment, and self-efficacy towards HIIT as displayed in Fig. 1.

### Grounding theories

The theory of expanded, extended, and enhanced opportunities states that more physical activity can be accrued if students are provided with more opportunities, more time for these opportunities and higher quality opportunities for routine physical activity [21]. In line with this theory, *Making a HIIT* aims to enhance HPE lessons by introducing curriculum content targeting high-intensity physical activity and using co-design, which could potentially enhance student engagement throughout the intervention [21]. *Making a HIIT* also includes components that support the basic psychological needs (autonomy, competence, and relatedness) described within self-determination theory (SDT), including the co-design process, exercise modifications, and partner and group workouts [22, 23]. The combined use of these two theories to inform the study aim to support meaningful opportunities for physical activity and foster students’ motivation to participate.

### Recruitment and participants

Schools in greater Brisbane will be recruited to *Making a HIIT* through purposeful sampling. Schools with known contacts will be identified and contacted one by one until three schools agree to participate. The aim is to consecutively recruit one co-educational school, one boys’ school, and one girls’ school. The first school will be used as a pilot school to trial the co-design lessons and adapt them if needed before starting in the next two schools. It will include all of the phase one activities and the questionnaires pertaining to students’ motivation, enjoyment, and self-efficacy towards HIIT. The range of included schools aims to help understand potential sex and school-based differences to comprehensively evaluate the integration of co-designing HIIT within HPE.

The head of the HPE department and HPE teachers will be informed of the study and will be involved in class selection for the study. Interested teachers will need to provide informed consent to participate. All students in the classes of consenting teachers will be eligible to participate as *Making a HIIT* will be conducted as part of the curriculum. However, only students who provide parental consent and student assent will have their data collected as part of the study. Students will be excluded if they are unable to participate in the HIIT workouts due to injuries or other reasons. Students will be in either Year 7 or Year 8 (aged 12–14 years) as these 2 years share the same curriculum content descriptions [15]. The flexibility of using Year 7 or 8 allows schools to meaningfully integrate the work conducted as part of the study in their curriculum according to their local needs.

Within each school, *Making a HIIT* will recruit three groups of participants: Group 1) HPE classes involved in the co-design of the HIIT workouts in phase one and who use the HIIT workouts in phase two (Co-Designers); Group 2) HPE classes that use the HIIT workouts in phase two but are not involved in the co-design (HIIT only); and Group 3) HPE classes that continue normal HPE lessons in phase two and are not involved in the co-design (control group). In the pilot school, only one class will be recruited for each group. In the second and third school, two classes will be recruited for each group.

### Sample size calculation

The sample size calculation was based on the main outcome of phase two, which is cardiorespiratory fitness using the 20-m shuttle run test (20mSRT). An achievable and meaningful difference has previously been reported as between 5 and 6 laps in adolescents for HIIT-based interventions [24, 25]. Six laps will be used in this study. The standard deviation of the 20 m SRT test was 22 laps in a sample of 100 school children aged 13–15 years [24]. Using 3 groups, an α of 0.05, and a power of 80%, we anticipate needing 44 students in each of the three groups based on a G*Power (Version 3.1) calculation (Critical F = 3.066, df = 2) [26]. Based on expected recruitment rates (75–80%), typical class sizes (25–30 students), attrition (5%), and data loss due to absence or abstaining from specific measures (10–15%) [17, 24, 27], two classes will be recruited to each group in schools two and three.

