### Data analysis

Data entry will be completed by one researcher with at least 10% checked by a second researcher. All data will be checked prior to analysis using range to assess any outliers or errors in data entry. To describe the population, descriptive statistics will be reported for each school separately. To determine the effect of the HIIT intervention on cardiorespiratory fitness, muscular fitness, and executive function, general linear models will be used to assess changes in the dependent variables with group (HIIT or control), timepoint, and group x time interaction included as independent variables. To determine the effect of involvement in co-design on students’ motivation, enjoyment, self-efficacy, feelings, and basic psychological needs, generalised linear models will be used to assess changes in the dependent variable, with group (Co-Design or not), timepoint, and group x time interaction included as dependent variables. Potential covariates, such as sex, age, BMI, involvement in co-design, baseline physical activity levels, baseline physical activity enjoyment, and baseline levels of the dependent variable will be identified using two-by-two tests and included in the model where appropriate.

The implementation of *Making a HIIT* will be evaluated using the Framework for Effective Implementation [20] across 8 components: 1) program reach – number of consenting schools and students; 2) dosage – number of HIIT workouts delivered and completed; 3) fidelity – students’ heart rate and RPE during HIIT workouts; 4) quality – variation in heart rate between students; 5) monitoring of control group – via heart rate; 6) responsiveness – student enjoyment and teacher perspectives; 7) adaption – modifications of the HIIT workouts by teachers; 8) differentiation – uniqueness of study.

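### The 44 per group is reproduced by entering 6/22 = 0.273, a two-mean standardised difference, as Cohen's f; for a 6-lap difference an unadjusted three-group F test of that size has about 19–24% power, not 80%

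*Protocol article*

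**What the plan says.** All of the sizing is in the article's section on sample size calculation.

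- Outcome: "The sample size calculation was based on the main outcome of phase two, which is cardiorespiratory fitness using the 20-m shuttle run test".
- Target difference: "Six laps will be used in this study".
- Variability: "The standard deviation of the 20 m SRT test was 22 laps in a sample of 100 school children aged 13–15 years". This is the SD of the test score. No SD of change and no pre–post correlation is given.
- Result: "Using 3 groups, an α of 0.05, and a power of 80%, we anticipate needing 44 students in each of the three groups", from a "G*Power (Version 3.1) calculation (Critical F = 3.066, df = 2").
- The number of classes is then set from expected recruitment (75–80%), class size (25–30), "attrition (5%), and data loss due to absence or abstaining from specific measures (10–15"%). That gives two classes per group in each of schools two and three.

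The phase two section on data analysis plans a different comparison from the three-group test: "general linear models will be used to assess changes in the dependent variables with group (HIIT or control), timepoint, and group x time interaction". It also lists the baseline level of the outcome among the potential covariates.

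**The concern.** A difference of 6 laps against an SD of 22 is a small effect, yet 44 students per group is a size normally associated with a medium one. G*Power's F tests take Cohen's f, the SD of the group means divided by the within-group SD. With three groups, f is always well below the standardised difference between the two most distant groups. If that difference was entered in place of f, the noncentrality is overstated several-fold and the stated power does not follow from the stated difference and SD.

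At stake is the claim that the study has 80% power for 6 laps on its main phase two outcome. On the stated difference and SD, the three-group test was in effect sized for a difference more than twice as large as the 5 to 6 laps that the article calls achievable and meaningful.

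**Working it through.** **Inputs from the sample size section:** difference 6 laps, SD 22, three groups, α = 0.05, power 80%, 44 per group (N = 132), critical F 3.066 with numerator df 2.

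**1. Reproduce the stated figure.** d = 6/22 = 0.2727. Enter this as f in a one-way F test, with λ = N·f², df1 = 2 and df2 = N − 3:

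| N | λ | Critical F | Power |
|---|---|---|---|
| 132 | 132 × 0.0744 = 9.82 | 3.0664 | 0.798 |
| 133 | 133 × 0.0744 = 9.89 | 3.0658 | 0.801 |

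N = 133 is 44.3 per group. Both the 44 and the critical F are matched within rounding.

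**2. The f that corresponds to 6 laps.** f = √(mean squared deviation of the group means) / SD.

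- Means 0, 6, 6 (both HIIT groups 6 above control): deviations −4, 2, 2; √(24/3)/22 = 2.828/22 = 0.129. This is the largest f possible when the range is 6.
- Means 0, 3, 6: deviations −3, 0, 3; √(18/3)/22 = 2.449/22 = 0.111. This is the smallest.

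The noncentrality in step 1 is therefore too large by (0.2727/0.1286)² = 4.5 to (0.2727/0.1113)² = 6.

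**3. Unadjusted three-group F test with the correct f.**

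| Means | f | λ at N = 132 | Power at 44 per group | n per group for 80% | Difference detectable with 80% at 44 per group |
|---|---|---|---|---|---|
| 0, 6, 6 | 0.129 | 2.18 | 0.24 | 196 | 12.8 laps |
| 0, 3, 6 | 0.111 | 1.64 | 0.19 | 261 | 14.7 laps |

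The last column comes from the f needed at N = 132, which is 0.2733: 0.2733 × 22 × 3/√2 = 12.8 and 0.2733 × 22 × √6 = 14.7.

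**4. A second route to 44.** A repeated-measures group-by-time calculation with two time points has λ = 2N·f²/(1 − ρ). With f = d/2 = 0.136 and an assumed ρ = 0.5, λ = 2N × 0.0186/0.5 = N × 0.0744, identical to step 1. The correct interaction f for a 6-lap difference in change is half the values in step 2, that is 0.056–0.064, and power at that correlation is again 0.19–0.24. The mis-scaling is the same.

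**5. The planned contrast at the expected yield.** Each group has four classes in schools two and three. Analysable students per group:

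- low: 4 × 25 × 0.75 × 0.95 × 0.85 = 60.6
- high: 4 × 30 × 0.80 × 0.95 × 0.90 = 82.1

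For pooled HIIT (2n) against control (n), the noncentrality of the t test is (6/22)·√(2n/3)/√(1 − ρ²). Here ρ is the pre–post correlation used by ANCOVA, an assumption because the article gives none. There is no allowance for clustering by class.

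| n per group | Unadjusted | ANCOVA, ρ = 0.7 | ANCOVA, ρ = 0.8 |
|---|---|---|---|
| 44 | 0.31 | 0.54 | 0.69 |
| 61 | 0.41 | 0.68 | 0.82 |
| 82 | 0.52 | 0.80 | 0.92 |

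**The case against.** The strongest reply is that the three-group test at 44 per group is not the trial that will be run. This stands as far as it goes. The planned analysis pools the two HIIT groups, may use baseline as a covariate, and should have 61–82 per group. Under favourable assumed correlations that contrast reaches or passes 80% before clustering. A reader might infer from the 19–24% that the planned trial has only about a fifth to a quarter power. The documents do not support that, because the figure belongs to an unadjusted three-group test (or a change-score interaction at correlation 0.5) with 44 per group.

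A reader might also infer that using d as f is the only way to reach 44, or that the article says this was done. Neither holds. Step 4 shows another route. The critical F fixes only the degrees of freedom: an ANCOVA with one covariate and N = 133 has the same value. The entered effect size, the type of test and any correlation are not stated. The reproduction is also not exact, since equal groups need 45 each for a full 80%. Entering d as f is a strong inference from the match.

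Nor does the article set any rule that a non-significant result would count against a meaningful effect, so that consequence should not be asserted.

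None of this rescues the stated figure. The article claims no correlation and presents 22 as the SD of the test itself. For the three-group test at 44 per group to reach 80%, the correlation would have to be about 0.88–0.91 in ANCOVA or 0.89–0.92 with change scores.

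**Conclusion.** The statement of 80% power with 44 per group for 6 laps is wrong as written. On the stated difference and SD, the unadjusted three-group F test has 19–24% power, needs 196–261 per group for 80%, and at 44 per group can detect about 12.8–14.7 laps. This rests on equal groups, SD 22 and a largest between-group difference of 6 laps. The range covers every possible position of the third group.

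The error lies in the justification of the sample size and does not show that the planned comparison is hopeless. Whether that comparison reaches 80% depends on a pre–post correlation that the article does not give, and on clustering, which would lower every figure in step 5.

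**What to change.** Rewrite the sample size paragraph, leaving enrolment unchanged:

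1. Replace the effect size by the f that matches 6 laps (0.111–0.129), or size directly on the mean difference and SD.
2. Withdraw the statement of 80% power for 6 laps with 44 per group.
3. Report instead the power, or the smallest detectable difference, for pooled HIIT against control with baseline adjustment, at the expected yield of about 61–82 per group.
4. Show this over a stated range of assumed pre–post correlations, with the source of any value relied on, and say whether clustering by class is allowed for.

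The cost is one rewritten paragraph and a less favourable stated power. No extra students, classes or measurements are needed.

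### The 44 per group matches 6/22 used as Cohen's f; with the stated 6 laps and SD of 22, the same F test has about 19–24% power, not 80%

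*Protocol article*

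**What the plan says.** The Sample size calculation section names the 20 m shuttle run test as the main outcome of phase two. It gives the target difference ("Six laps will be used in this study") and the variability ("The standard deviation of the 20 m SRT test was 22 laps in a sample of 100 school children aged 13–15 years"). The design inputs are "Using 3 groups, an α of 0.05, and a power of 80"%. The result is "we anticipate needing 44 students in each of the three groups based on a G*Power (Version 3.1) calculation", with the output reported as "Critical F = 3.066, df = 2". The section prints no effect size f, no pattern of group means, no pre-post correlation and no allowance for classes.

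Attrition of 5% and data loss of 10–15% are then used, with class size and recruitment rate, to justify two classes per group in schools two and three.

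The phase two Data analysis section plans general linear models for the fitness outcomes "with group (HIIT or control), timepoint, and group x time interaction included as independent variables". The baseline value appears there only as one of several potential covariates.

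**The concern.** A two-group difference divided by an SD is Cohen's d. The effect size for a three-group F test is Cohen's f, which is always smaller than d when d is taken across the full range of the means. Entering d in the f field inflates the effect more than twofold and shrinks the required sample by a factor of four to six. The printed 44 and critical F look like the product of that substitution.

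The test that was powered is also not the contrast in the analysis section: a three-group F test with 2 numerator df against a two-level HIIT-or-control comparison with 1 df.

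The stated power is what a reader will use to interpret a null shuttle run result. If it is wrong, a non-significant finding could be taken as evidence against a 6-lap benefit that the calculation never had a good chance of detecting.

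**Working it through.** **Inputs (Sample size calculation section).** Difference 6 laps; SD 22 laps; 3 groups; α = 0.05; power 80%; 44 per group (N = 132); critical F = 3.066 with 2 numerator df.

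**Method.** Three-group F test: λ = N·f², df = (2, N − 3), power = P[noncentral F > critical F].

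**1. Reproducing the plan's figure.** Put f = 6/22 = 0.2727.
- N = 132: λ = 132 × 0.2727² = 9.82, critical F(2, 129) = 3.0664, power 79.8%.
- N = 133: critical F(2, 130) = 3.0658, power 80.1%; 133/3 = 44.3 per group. One added covariate returns the critical F to 3.0664 with power still 80.1%.

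Both the 44 and the 3.066 are recovered.

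**2. The f that 6 laps and SD 22 imply.** f = SD(group means)/22, where the SD of the means uses divisor 3.

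| Group means (laps) | SD of means | f | λ at N = 132 | Power at 44 per group | N for 80% |
|---|---|---|---|---|---|
| 6, 6, 0 (largest f for a 6-lap range) | 2.828 | 0.129 | 2.18 | 23.8% | 588 (196 per group) |
| 6, 3, 0 (smallest f) | 2.449 | 0.111 | 1.64 | 18.8% | 783 (261 per group) |

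The f that was evidently used is 0.2727/0.1286 = 2.1 to 0.2727/0.1113 = 2.4 times too large.

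**3. What 132 students can detect.** 80% power at N = 132 needs f = 0.2733, so the SD of the means must be 0.2733 × 22 = 6.01 laps. For a range R the SD of the means is 0.4714R (both HIIT groups equal) or 0.4082R (evenly spaced). R = 6.01/0.4714 = 12.8 laps, or 6.01/0.4082 = 14.7 laps.

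**4. The contrast in the analysis section.** Pooled HIIT against control, two-sided t test, d = 6/22, 88 v 44: power 31.1%.

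**5. At the planned recruitment.** Four classes per group (two in each of schools two and three), using the protocol's ranges:
- low: 4 × 25 × 0.75 × 0.95 × 0.85 = 60.6 per group
- high: 4 × 30 × 0.80 × 0.95 × 0.90 = 82.1 per group

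Unadjusted power is then 25–42% for the three-group test and 41–52% for the pooled contrast.

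**6. Baseline adjustment (the correlation r is an assumption; the protocol gives none).** The residual SD becomes 22·√(1 − r²). Clustering is ignored here.

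| r | Three-group test (6, 6, 0), 44 per group | Pooled, 88 v 44 | Pooled, at 61–82 per group |
|---|---|---|---|
| 0.7 | 43% | 54% | 68–80% |
| 0.8 | 58% | 69% | 82–92% |

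At 44 per group, 80% needs r of about 0.88 for the three-group test with means 6, 6, 0, since √(1 − (0.1286/0.2727)²) = 0.882; about 0.91 with means 6, 3, 0; and about 0.85 for the pooled contrast.

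**7. Illustration with classes as clusters (assumed ICC 0.05).** There are 8 HIIT and 4 control classes of m = 15–20 evaluable students. The design effect is 1 + (m − 1) × 0.05 = 1.70 to 1.95, applied to the baseline-adjusted variance, with t on 12 − 2 = 10 df. Example for m = 20, r = 0.8: SE = √[484 × 0.36 × 1.95 × (1/160 + 1/80)] = 2.52; 6/2.52 = 2.38; power 57%. Over m = 15–20 the power is 39–44% at r = 0.7, 51–57% at r = 0.8 and 78–84% at r = 0.9.

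**The case against.** The best reply has four parts.

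**The f is not printed.** The substitution of d for f is therefore inferred. Another route leads to the same noncentrality: a repeated-measures interaction with f = d/2 = 0.136 and correlation 0.5 gives λ = 132 × 2 × 0.136²/0.5 = 9.82. This stands as a caution about mechanism only. That route overstates the effect too, because the interaction f for means 6, 6, 0 is 0.1286/2 = 0.0643, giving λ = 2.18 and again 23.8%. An adjusted f of 0.27 would also arise with r of about 0.88, but no such r is stated.

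**The 19–24% is not the power of the trial.** It belongs to an unadjusted three-group test on the 22-lap SD, whereas the study measures before and after and may adjust for baseline. This is right, and the figure should be read as the power of the calculation as written. The power of the planned analysis depends on a correlation and an ICC that the protocol does not give.

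**More than 44 per group are expected.** With 61–82 per group, baseline adjustment and r = 0.8, the pooled contrast would exceed 80% if classes did not matter. This is also right. It shows that the recruitment may be adequate under favourable assumptions, not that the printed calculation is correct.

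**The test mismatch is softer than it looks.** Involvement in co-design is a listed covariate, and together with HIIT-or-control it separates all three groups. That is fair, but the model still names a two-level group factor, and a three-group analysis would not restore the 80%.

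**Conclusion.** The concern holds. The stated 6 laps, SD of 22 and 44 per group do not give 80% power for the stated three-group F test; they give 18.8–23.8%, depending on where the middle mean lies. The 44 per group has 80% power for about 12.8 to 14.7 laps on that test, more than twice the difference the protocol calls achievable and meaningful. For pooled HIIT against control the figure at 44 per group is 31%.

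These results rest only on the protocol's own difference, SD, α and group sizes, with students treated as independent. That d was entered as f is an inference, though both printed outputs match it; the conclusion does not depend on it. Power for a baseline-adjusted analysis cannot be settled from the document. It ranges from well below 80% to above it, according to the assumed correlation, ICC and yield. The point should be corrected because it concerns the main outcome and the stated power is wrong as written.

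**What to change.** Replace the 80% statement with a calculation for the contrast to be tested: pooled HIIT against control, adjusted for baseline laps, with classes as clusters. State the assumed pre-post correlation and ICC with their sources, and show a range for each. Report the power for 6 laps, or the detectable difference, at the expected 61–82 evaluable students per group. Say in the analysis section whether the primary comparison has two or three groups, so that it matches the calculation.

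If nothing else is changed, the text should say that 44 per group gives 80% power, on the unadjusted three-group test, for a difference of about 13–15 laps rather than 6.

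The cost is one rewritten paragraph and a less favourable power figure. Recruitment and data collection are unaffected.
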